Interdisciplinary multimodal pain therapy (MPT) describes the simultaneous, comprehensive treatment in which various somatic, physical and psychological interventions are integrated according to a predefined treatment plan with an identified therapeutic goal. The treatment is provided in small groups with a maximum of eight patients by a team of therapists consisting of physicians, psychologists or psychotherapists and other disciplines such as physiotherapists and others.^14^ MPT is currently considered the gold standard in pain management and treatment for patients with chronic or potentially chronic back pain.^15^ The efficacy of interdisciplinary MPT in the treatment of chronic or recurrent back pain with risk of chronification has already been proven in various studies.^8 13 14 16–20^ The term recurrent describes pain episodes that reoccur after a symptom-free period of at least 6 months.^8^ Chronification, moreover, describes the transition from temporary to permanent, or chronic, back pain. After successful MPT, patients usually return to the monodisciplinary treatment of their general practitioner or orthopaedist. As a result, the risk of recurrence remains with the end of MPT. The goal of this new approach to the treatment of back pain is to achieve sustainability of MPT by combining MPT with relapse prophylaxis (RP). Thus, what is learnt during multimodal treatment in terms of physical activity and lifestyle can be applied to everyday life in the long term.

The intervention examined in this study, the 12-month RP programme, immediately follows the 4-week MPT. Like the MPT, the RP will be performed by the Rehabilitation Center, Bad Zwischenahn, on an outpatient basis. The rehabilitation centre is completely independent of the evaluating institution. The RP aims not only to provide prophylaxis against chronifying back pain relapses but also to support life-integrated physical activity. RP is the all-important link between the curative MPT phase beforehand and the patient’s physical activity afterwards. The patient will be assigned to one of three RP paths at the end of the MPT as part of an assessment during the interdisciplinary rounds and team meetings. The paths correspond to RP programmes with three different intensities (low, medium and high) for which the patient will be selected based on the severity of his or her complaints (see figure 1).

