## Methods and analysis

### Study design

In order to answer the research questions, outcome, process and health economic analyses will be carried out. Different research methods will be used for this purpose. The comparative population will be formed by randomising the groups of participants. The division into the respective groups (intervention group, IG or control group, CG) will be carried out monthly to ensure that the patients of both groups are not able to exchange information with each other. Patients who start an MPT simultaneously in the Rehabilitation Center each form a cluster. These clusters will be randomised to the IG or CG (see figure 2). The evaluator will inform the Rehabilitation Center monthly via email in the third week of the MPT whether the group is an IG or CG. Up to this point, neither the patient nor the treatment staff will know which group the patient belongs to. The recruitment period will be 24 months.

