### Sample size calculation

The case number calculation was carried out for the primary outcome days of incapacity to work. Currently, the described patient group of AOK-insured persons has an average number of 37 days off work (SD: 58) per year. It is assumed that the average number of 37 days off work per year will decrease in the IG by 40% (or 15 days) compared with the CG. This results in an effect size of d=0.3409275. To test with a power of 80% (1−ß=0.8) and a significance level of 5% (ɑ error=0.05), a case number of 137 subjects per group is required for significant proof of the expected effect. The number of cases was calculated using the software G*Power (see online supplemental figureS2).

Taking an intraclass correlation coefficient of 0.01 and a design effect of 1.1 at an average cluster size of 15.3 (22×16+2×8) into account, the required number of cases is 293 subjects, that is, 147 subjects per group.^29–32^ Considering a drop-out of 10% for patients who drop out during the MPT, that is, before randomisation, results in a required total case number of 322. The available population covers the required case number (see figure 3 and online supplemental figure S2).

10.1136/bmjopen-2022-067412.supp2Supplementary data

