#### Primary outcome

The data will be analysed by reference to the primary outcome (days of incapacity to work), which is carried out by intention-to-treat analysis. Patients are analysed according to their original group assignment.

To test the primary hypothesis H_1_ ‘The intervention reduces the number of days of incapacity to work’, an analysis of covariances with cluster adjustment will be performed, using a significance level of 0.05. Covariables included into the model will be age, gender and comorbidities (eg, depression). In addition, a hypothesis test (two-sided t-test with a significance level of 0.05) will be performed.

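### Drop-out during the four-week MPT is counted as pre-randomisation although allocation is disclosed in week 3, so the status of late MPT leavers in the intention-to-treat set is contradictory

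*Protocol article*

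**What the plan says.** All statements are in the protocol article.

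- **Introduction:** "the 12-month RP programme, immediately follows the 4-week MPT". MPT thus lasts four weeks, and relapse prophylaxis (RP) starts when it ends.
- **Study design:** patients who start MPT together form a cluster, and clusters are randomised to the intervention group (IG) or control group (CG). On timing: "The evaluator will inform the Rehabilitation Center monthly via email in the third week of the MPT whether the group is an IG or CG". On concealment: "Up to this point, neither the patient nor the treatment staff will know which group the patient belongs to".
- **Sample size calculation:** after the allowance for clustering, "the required number of cases is 293 subjects, that is, 147 subjects per group". The last step reads "Considering a drop-out of 10% for patients who drop out during the MPT, that is, before randomisation" and "results in a required total case number of 322".
- **Primary outcome (under Quantitative analysis):** the analysis is by intention to treat, and "Patients are analysed according to their original group assignment".
- **Outcome evaluation** counts the primary outcome, days off work, over the year that begins when MPT ends. **Strengths and limitations** says that it comes from claims data, not questionnaires.

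**The concern.** Loss during MPT equals loss before randomisation only if allocation comes after MPT has finished. Study design places the disclosure one to two weeks earlier. Someone who leaves late in week 3 or in week 4 leaves after the arm is known at the centre, yet the sample size section classes that person as never randomised.

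The classification matters because it decides whom the intention-to-treat promise covers. A patient labelled pre-randomisation has no assigned group and drops out of the comparison without any visible breach of that promise. The outcome window makes this easier, since it starts at the end of MPT and the article gives no such date for a patient who leaves early.

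Leaving after disclosure could also depend on the arm. CG patients have nothing further to expect from the trial, whereas IG patients are about to be placed on an RP path. If leaving is related both to arm and to later days off work, removing leavers is a post-randomisation exclusion that randomisation cannot correct.

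**Working it through.** **1. The plan's own figure.** 293 × 1.10 = 322.3, the stated 322. (Dividing instead, 293 / 0.90 = 325.6, gives 326, a difference of about 1%.) The drop-out step reproduces. The issue is when the loss occurs, not the arithmetic.

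**2. The statements side by side.**

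| Section | What it implies for a patient who leaves in week 4 |
|---|---|
| Study design | The arm has already been sent to the centre |
| Sample size calculation | The patient left before randomisation |
| Primary outcome | If assigned to a group, the patient is analysed in it |

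The first two cannot both hold. The article does not say on which day the allocation is generated. If it is generated at the time of the e-mail, losses after the e-mail follow randomisation. If it is generated earlier and only disclosed in week 3, still more of the losses follow randomisation. Losses before disclosure cannot depend on the arm as long as concealment holds, so disclosure is the time that matters for bias.

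**3. How many patients.** The article gives no timing of drop-out. Assume that the 10% is spread evenly over four weeks, which is 10% / 4 = 2.5% of starters per week. Total loss is 322 × 0.10 = 32.2.

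- Disclosure at the end of week 3 (one week left): 32.2 × 0.25 = 8.05, about 8 patients.
- Disclosure at the start of week 3 (two weeks left): 32.2 × 0.50 = 16.1, about 16 patients.

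As a share of those still in MPT at disclosure: 8.05 / (322 − 32.2 + 8.05) = 8.05 / 297.85 = 2.7%, and 16.1 / (322 − 32.2 + 16.1) = 16.1 / 305.9 = 5.3%.

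**4. How far an arm mean could move.** Let a fraction p of one arm be excluded, and let those patients have on average D more days off work than the patients who remain. The arm mean then falls by p × D. Both values are assumed: p = 2.5–5%, D = 20–58 days (58 is the article's SD, used only as an upper mark).

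| p | D = 20 | D = 58 |
|---|---|---|
| 2.5% | 0.5 days | 1.45 days |
| 5% | 1.0 days | 2.9 days |

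If D is measured from the mean of the whole arm, the shift is p × D / (1 − p), which gives 0.51 days at the low end (0.025 × 20 / 0.975) and 3.05 days at the high end (0.05 × 58 / 0.95). The range is roughly 0.5 to 3 days. Against the planned 15 days, 0.5 / 15 = 3% and 3 / 15 = 20%.

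**5. Both arms and direction.** The shift in the group difference is p × D in CG minus p × D in IG. Equal products cancel. If only CG patients with many days off are removed, the CG mean falls and the result moves against the intervention. If such patients are removed only from IG, it moves in favour. If leavers are people who have already recovered, both signs reverse.

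**The case against.** A reader might infer that the plan will exclude late leavers and that the primary comparison is therefore biased. The article does not say so. The sentence in question is a recruitment allowance that takes 293 to 322, not a definition of an analysis set. The only statement on who is analysed is the intention-to-treat one, and read literally it keeps these patients. The article also refers to a separate analysis plan and to a flow diagram that are not available here, and either may settle the matter. This stands: exclusion is possible under the text, not announced by it.

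A reader might also take it as given that patients learn their arm in week 3. The article says that the centre is informed then, and that nobody at the centre knows before. That patients are told at once is implied but not stated.

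The figures above are deliberately unfavourable. They remove patients from one arm only, and the excess of 20 to 58 days has no source in the article. An even spread of drop-out also fits poorly with departures prompted by disclosure. These points stand, and they limit what can be said about size.

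Finally, the T1 questionnaire at the end of MPT may be answered with the arm known, but the primary outcome comes from claims data and does not use T1. That aspect is secondary.

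None of this removes the contradiction. The request is not for detail that belongs in an analysis plan: a stated premise of the sample size section is incompatible with the stated design.

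**Conclusion.** The point holds as an inconsistency to be reconciled before analysis. The article supports two analysis sets, one with and one without the patients who leave between disclosure and the end of MPT, and the choice between them should not be left open until data are seen. That the intention-to-treat comparison is biased cannot be concluded.

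The likely size is modest: about 8 to 16 of 322 starters if drop-out is even over four weeks, and a shift of roughly 0.5 to 3 days in one arm's mean under one-sided loss with an assumed excess of 20 to 58 days. The direction is unknown, and similar losses in both arms would largely cancel. The correction is still worth making because it protects the primary comparison at almost no cost.

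**What to change.** 1. **Define the analysis set.** The intention-to-treat set is every patient still enrolled in the cluster when the allocation e-mail is sent, analysed in that cluster's arm. Days off work are counted in claims data for 12 months from the cluster's scheduled MPT end, whether or not the patient completes MPT. This also gives early leavers a start date.
2. **Reword the drop-out sentence in Sample size calculation.** The 10% should cover only patients who leave MPT before allocation is disclosed, with a statement that later leavers remain in the analysis. Merely replacing the reference to randomisation by one to disclosure, while still speaking of all loss during MPT, would repeat the error.
3. **Optional, where lead time for RP allows:** disclose the allocation only at the end of MPT, after T1 has been completed. This would make the present sentence true and keep T1 and the whole of MPT blind.

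Cost: items 1 and 2 are one definition and one sentence. No new data collection is needed, because claims data do not depend on completing MPT; patients who withdraw consent to data use would have to be reported separately. Item 3 leaves less time to organise the first RP contacts, which matters because RP follows MPT without a gap.

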**Figure 3 F3:**
[figure not shown]
CONSORT flow diagram. CONSORT, Consolidated Standards of Reporting Trials.

### Statistical analysis

Statistical analysis is performed on the basis of a defined analysis plan. If there are justified deviations from this plan, these will be documented and reported in subsequent publications. Compared with the original plan, the one-sided test with regard to hypothesis H_4_ was changed to a two-sided test, as this seems reasonable.

### Qualitative analysis

The qualitative guided interviews will be documented by means of audio recordings. The recordings will be transcribed without personal information (eg, name and place of residence). The evaluation of the guided interviews will be based on the qualitative content analysis according to Mayring and carried out with the help of the MAXQDA software.^33^

### Quantitative analysis

All patient-related data will be pseudonymised by assigning a unique identification number. A plausibility check of the data will be carried out. Initially, descriptive analysis of the data will be performed. Sample characteristics will be analysed with regard to their distribution in the two groups by means of the χ^2^ test for binary variables and Mann-Whitney-U test for continuous variables.

#### Primary outcome

The data will be analysed by reference to the primary outcome (days of incapacity to work), which is carried out by intention-to-treat analysis. Patients are analysed according to their original group assignment.

To test the primary hypothesis H_1_ ‘The intervention reduces the number of days of incapacity to work’, an analysis of covariances with cluster adjustment will be performed, using a significance level of 0.05. Covariables included into the model will be age, gender and comorbidities (eg, depression). In addition, a hypothesis test (two-sided t-test with a significance level of 0.05) will be performed.

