### Multimodal pain therapy

Employees of the AOK Lower Saxony will contact the potentially eligible insured and refer them to the Rehabilitation Center. Before starting MPT, a comprehensive initial examination will be performed by orthopaedists, physiotherapists and psychologists. The MPT programme intensity depends on the severity of the back pain. Patients in the standard MPT group will be treated for 3–4 hours per day, 4 days a week, while patients in the complex MPT will be treated for 5–7 hours per day, 5 days a week. Two groups of eight patients each will be conducted in parallel. The complex therapy group will provide additional treatment and place more emphasis on psychological and medical intervention aspects, while patients in the standard group will be advised to exercise on their own during these times. Overall, it is expected that patients will benefit from the structured approach of the programme.

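### The primary ANCOVA omits standard versus complex MPT, a severity-based factor fixed before allocation, and so gives up some precision

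*Protocol article*

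**What the plan says.** All points are from the protocol article.

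- **Two programmes.** Under Multimodal pain therapy: "Patients in the standard MPT group will be treated for 3–4 hours per day, 4 days a week", whereas "patients in the complex MPT will be treated for 5–7 hours per day, 5 days a week".
- **Chosen by severity.** The same section says: "The MPT programme intensity depends on the severity of the back pain". It also says: "Before starting MPT, a comprehensive initial examination will be performed".
- **Allocation comes later.** Under Study design, the evaluator tells the centre "in the third week of the MPT whether the group is an IG or CG", and until then neither patients nor treating staff know the arm. The Sample size calculation agrees on the order: "Considering a drop-out of 10% for patients who drop out during the MPT, that is, before randomisation".
- **Unit of randomisation.** "Patients who start an MPT simultaneously in the Rehabilitation Center each form a cluster". No stratification by MPT programme is described.
- **The factor is examined elsewhere.** The Process evaluation section will look at how participants were assigned to the standard and complex programmes.
- **Primary model.** A cluster-adjusted analysis of covariance at the 0.05 level, for which "Covariables included into the model will be age, gender and comorbidities (eg, depression"). The example in brackets qualifies comorbidities only. The Measurements section brings education and quality-of-life data into the analysis in general terms, but not MPT programme.

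**The concern.** MPT programme marks two things that plausibly predict later incapacity: how severe the back pain was judged to be at entry, and how much background treatment the patient received. It is fixed before the arm is known, so adjusting for it carries no risk of conditioning on a consequence of allocation. It will also be available, since the process evaluation uses it.

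The listed covariates carry no back-pain severity measure at all. A prognostic factor left out of the model adds to the residual variance. With only about 24 randomised units, any chance difference between the arms in the share of complex patients also stays in the estimate. What is at stake is precision, in a trial whose outcome is very variable (mean 37 days, SD 58).

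This is not a detail that the article leaves to its analysis plan. The article states the covariate list, and the point concerns that stated choice.

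**Working it through.** **Inputs from the article.** Hours and days per week (Multimodal pain therapy); SD 58, target 15 days, d = 0.3409275, 137 per group, intraclass correlation 0.01 (Sample size calculation).

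**Assumptions.** The article gives neither the share of complex patients nor the difference in incapacity days between programmes. I take a 50:50 split and differences D of 10, 20 and 30 days.

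**1. The plan's own figure.** With two-sided alpha 0.05 and 80% power, n per group = 2 × (1.960 + 0.842)² / 0.3409275² = 135.06, so 136 by the normal formula. The exact t-test calculation gives 136.02, rounded up to the stated 137. The figure is reproduced from the stated d. That d does not follow from 15 days and SD 58, which give 15/58 = 0.259; this is a separate matter. The steps below use the stated 15 days and SD 58, which is why baseline power is below 80%.

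**2. Contrast between programmes.**
- Standard: 3–4 h × 4 days = 12–16 h per week.
- Complex: 5–7 h × 5 days = 25–35 h per week.
- Ratio: 25/12 = 2.08 at the low ends, 30/14 = 2.14 at the midpoints, 35/16 = 2.19 at the high ends. The extreme pairings are 25/16 = 1.56 and 35/12 = 2.92.

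**3. Variance explained.** At 50:50, R² = (D/2)² / 58².
- D = 10: 25/3364 = 0.7%
- D = 20: 100/3364 = 3.0%
- D = 30: 225/3364 = 6.7%

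**4. Power by formula, before clustering.** Residual SD = 58 × √(1 − R²); SE = residual SD × √(2/137); power = Φ(15/SE − 1.960).

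| D (days) | Residual SD | SE (days) | Power |
|---|---|---|---|
| 0 (no gain) | 58.0 | 7.01 | 57.2% |
| 10 | 57.8 | 6.98 | 57.5% |
| 20 | 57.1 | 6.90 | 58.4% |
| 30 | 56.0 | 6.77 | 60.1% |

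The gain is 0.3, 1.2 and 2.9 points.

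**5. Simulation with clustering.** 24 monthly clusters of 16, intraclass correlation 0.01, SD 58, cluster-level comparison, 2,000 runs per setting.
- Type I error was 0.05–0.06 and the estimate was unbiased, with or without adjustment.
- With a mix that varies by month, power rose from 61.2% to 61.9% (D = 10), 59.9% to 60.5% (D = 20) and 60.2% to 63.8% (D = 30).
- With exactly 8 standard and 8 complex patients every month, the adjusted and unadjusted cluster-level results were identical.

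Steps 4 and 5 agree: about 1 point or less at 10 to 20 days, and about 3 to 4 points at 30.

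**The case against.** The strongest reply is that nothing is wrong here. Randomisation protects the comparison, chance imbalance is already covered by the test's error rate, and the choice of prognostic covariates is partly taste. As far as validity goes, this stands.

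A second reply is that the design may already balance the factor. The article describes two parallel groups of eight and then contrasts the complex and standard groups, so one of each per month is a natural reading. If that mix held exactly, cluster-level results would not change. This stands in part. No section fixes an 8:8 mix, 10% are expected to drop out before randomisation, and 368 is a maximum rather than a target. Even with exact balance, an individual-level ANCOVA without the factor leaves its variance in the residual and can slightly overstate the standard error, by at most 1/√(1 − 0.067) = 1.035, about 3.5%, at D = 30.

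A third reply is that the size rests on assumed differences. That is correct. Severity and treatment intensity could offset each other, and the net difference between programmes could be close to zero.

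Two stronger readings are tempting, and the article supports neither.

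- **Confounding of the arm comparison.** A reader might infer that the programme mix could distort the result materially. If 147 patients per arm fall independently 50:50, the SD of the imbalance is √(2 × 0.25/147) = 5.8 percentage points. At 10 to 30 days that is 0.6 to 1.7 days, against a standard error of 58 × √(2/147) × √1.1 = 7.1 days.
- **The single December course as a source of imbalance.** With full courses, one group of each type in the other months and 12 clusters per arm, the worst case is both Decembers of the same type in one arm: 96/176 versus 96/192 complex, or 4.5 points. At 20 to 30 days that is 0.9 to 1.4 days.

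**Conclusion.** The point holds as a matter of precision. The stated primary model leaves out a factor that is set by severity, fixed before allocation and examined elsewhere in the study, and it contains no substitute measure of back-pain severity. The comparison remains unbiased and the type I error is not inflated.

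The gain from adjustment is small: about 1 power point if the programmes differ by 10 to 20 incapacity days, and up to about 4 points at 30 days with a mix that varies by month. It is close to nothing if the difference is small. These figures rest on an assumed 50:50 split, SD 58 and assumed differences between programmes, none of which the article supplies except the SD. The recommendation is justified because the remedy costs almost nothing, not because the omission threatens the result.

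A reader might also infer that the secondary analyses share the fault, or that the plan should test whether relapse prophylaxis works differently after complex MPT. The article does not support either as an error. Functional capacity and costs are compared by two-sided t-tests, so there is no covariate model there from which the factor has been left out. A difference in effect by programme lies outside H1 to H4, and exploratory subgroup work is ordinarily left to the analysis plan.

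**What to change.** In the Primary outcome section and the analysis plan, add MPT programme as assigned at the start (standard versus complex) as a fixed covariate in the cluster-adjusted primary ANCOVA, alongside age, gender and comorbidities. Use the initial assignment even if a patient later changes programme, so that the covariate stays a pre-allocation variable.

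Make the change before outcome data are seen, since adding the term later would look data-driven. The cost is one sentence and one degree of freedom. No new data are needed, because the process evaluation already uses the assignment.
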